### **3.6.2 Data Analysis**

#### **3.6.2.1 Analysis Principles**

Categorical variables will be described as frequencies and percentages. Continuous variables will be summarized as means with standard deviations or as medians with interquartile ranges, based on their distribution. The primary outcome of hospitalization rate will be analyzed using generalized linear mixed models (GLMMs). Both unadjusted and adjusted estimates will be presented; adjusted analyses will include age, sex, comorbidities (including diabetes, hypertension, and cardiovascular disease), and baseline eGFR. Other secondary outcomes will be analyzed using the same approach but without adjustment for baseline eGFR.

For missing data, if the proportion of missingness is below 20%, continuous variables will be imputed using regression-based methods and categorical variables using predictive mean matching. Any variable with over 20% missing values will be excluded from the analysis.

All analyses will adhere to the intention-to-treat (ITT) principle. Given the pragmatic trial setting, a decline in adherence is anticipated. Should adherence to the CDSS intervention fall below 60%, a secondary as-treated (AT) analysis will be performed as pre-specified. All statistical analyses will be conducted using RStudio (v2022.02.03).

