#### **3.4.2 Randomization and Intervention Allocation**

Stratified cluster randomization is employed at center level. Prior to the study, the 30 centers are stratified into three categories based on annual outpatient visit volume: large ( $\geq 10,000$  visits/year), medium (1,000–9,999 visits/year), and small ( $< 1,000$

---

visits/year). Within these strata, an independent statistician uses a computerized system to randomly assign centers in a 1:1 ratio to the intervention group (CDSS plus usual care) or the control group (usual care alone). Randomization results are concealed until the start of the intervention assignment.

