## **3.6 Statistical Analysis**

### **3.6.1 Sample Size and Statistical Power**

The primary outcome is a composite hospitalization rate for kidney-related (acute kidney injury, progression of kidney disease, or requiring dialysis) or cardiovascular events (myocardial infarction, stroke, heart failure, or cardiovascular procedures). Based on data from the US CRIC cohort, the all-cause hospitalization rate for CKD patients is 35.0 per 100 person-years. The sample size calculation aims to detect a 20% reduction in this rate following 36 months of CDSS intervention, compared to usual care. The calculation is performed using cluster randomization tools (online calculator at <https://clustercts.shinyapps.io/rshinyapp/>) with the following parameters: 30 randomized centers (15 per arm), an intraclass correlation coefficient of 0.02, and a significance level of 0.05. A total sample size of 3,240 participants is estimated to provide 90% statistical power (**Figure 1**).

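### The primary GLMM rests on 30 centres with no small-sample method stated; an ordinary uncorrected fit would test at about 6–9% (Wald z) rather than 5%, and no deciding model is named

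*Protocol*

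**What the plan says.** Section 3.4.2 randomises whole centres within three visit-volume strata; a statistician will "randomly assign centers in a 1:1 ratio to the intervention group" or to control. Section 3.6.1 sets the design at "30 randomized centers (15 per arm), an intraclass correlation coefficient of 0.02, and a significance level of 0.05".

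On the analysis, section 3.6.2.1 states: "The primary outcome of hospitalization rate will be analyzed using generalized linear mixed models (GLMMs"). It then says: "Both unadjusted and adjusted estimates will be presented; adjusted analyses will include age, sex, comorbidities", with baseline eGFR also in the list. Secondary outcomes follow the same approach without baseline eGFR. RStudio is named as software.

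The section does not give the estimation method, the type of test, the reference distribution, the degrees of freedom or a small-sample correction, and it does not rule a correction out. It does not rank the two estimates. The visit-volume strata are not among the listed covariates. A separate rule in the same section drops any variable with more than 20% missing values.

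**The concern.** Every patient in a centre has the same allocation, so the evidence on the CDSS effect comes from 30 units, however many patients are enrolled. ML estimation tends to understate the between-centre variance with so few units, and a normal critical value ignores the uncertainty in that estimate. Both push the same way: the standard error or cut-off is too small, the interval too short, and a false positive more likely than 5%.

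The second issue is separate. Two estimates of the primary effect are planned and neither is ranked. If they fall on opposite sides of 0.05, the document does not say which one stands.

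**Working it through.** **Inputs.** From section 3.6.1: 30 centres, ICC 0.02, level 0.05 (sidedness not stated; two-sided assumed), 3,240 patients, so 3,240/30 = 108 per centre. The control rate is 0.35 per person-year ("the all-cause hospitalization rate for CKD patients is 35.0 per 100 person-years") and the aim is to "detect a 20% reduction in this rate following 36 months of CDSS intervention", so 0.35 × 0.8 = 0.28. Assumed, because the protocol does not give them: the composite event rate (0.35 is an all-cause rate), the between-centre standard deviation of the log rate, and the correlation between the two models.

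**The plan's own figure.** The protocol says: "A total sample size of 3,240 participants is estimated to provide 90% statistical power". The design effect is 1 + 107 × 0.02 = 3.14. Read as a 3-year Poisson rate comparison:

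- SE = √[((0.35 + 0.28)/3) × 3.14 / 1,620] = 0.0202, and 0.07/0.0202 ≈ 3.47.
- z reference: power = Φ(3.47 − 1.96) = 93.4%.
- t reference on 28 df (non-central t): power = 91.7%.

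The 91.7% is within 2 points of the stated 90%, but 3,240 is not reproduced exactly: 90% needs 2,220 patients with z and 2,670 with t on 28 df. Other readings, all with z, fall well short: one-year Poisson 52%, a binary 0.35 versus 0.28 68%, and 3-year cumulative risk (0.650 versus 0.568) 77%. The 3-year Poisson reading is therefore used for the cost of the fix.

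**Type I error, closed form.** Treat the centre log rates as roughly normal with equal centre sizes. An unbiased variance gives a t statistic on 28 df, or 26 with terms for the three strata. ML divides by 30 instead of the residual df.

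| Uncorrected test | Effective t cut-off, 28 df | Size, 28 df | Size, 26 df |
|---|---|---|---|
| z cut-off, unbiased variance | 1.960 | 6.0% | 6.1% |
| z cut-off, ML variance | 1.960 × √(28/30) = 1.893 | 6.9% | 8.0% |
| Likelihood ratio, ML | √[28 × (e^(3.841/30) − 1)] = 1.956 | 6.1% | 7.1% |

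The correct cut-off on 28 df is 2.048. The ML Wald z interval therefore has 1.893/2.048 = 0.92 of its proper width, about 8% too short.

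**Type I error, simulated null trials** (30 centres, mean 108 patients, 3 years):

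- Poisson GLMM in lme4, Wald z, rate 0.35 and log-SD 0.20: 7.1% with equal and 6.9% with unequal centre sizes (2,000 runs each).
- The same model with 1,150 runs each: 9.2% (rate 0.35, log-SD 0.14), 7.6% (rate 0.10, log-SD 0.26) and 6.5% (rate 0.10, log-SD 0.10). Monte Carlo standard errors are 0.7 to 0.9 points.
- Gauss-Hermite ML at 0.35 per year, ICC 0.02 or 0.05, 6,000 runs per setting: Wald z 7.0–7.2%. A restricted-likelihood variance on centre log rates with t on 26 df gave 5.0–5.2%.
- A further set of ML fits gave 6.3–6.7% for Wald z and 5.4–5.8% for the likelihood ratio.

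The 9.2% is the highest value and among the least precise. An ICC of 0.02 at 1.05 events per patient gives a variance of (0.02/0.98)/1.05 = 0.0194, a log-SD of 0.139. The Gauss-Hermite runs at that setting gave about 7%, so 9% is best taken as an upper end.

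**A t cut-off alone is not enough.** Applying the 28-df cut-off to the lme4 ML fits still gave 5.5–8.0%. The variance needs correcting as well.

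**Two models.** If success could be claimed on either result, each tested at an exact 5%, a bivariate normal calculation gives 6.5% at an assumed correlation of 0.95 and 8.4% at 0.70.

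**The case against.** The estimator, test and degrees of freedom are commonly left to a statistical analysis plan, and that document is not shown. A GLMM is compatible with every correction suggested here, so silence is not a decision against one. The protocol prescribes neither ML nor a Wald z test. Presenting unadjusted and adjusted estimates side by side is ordinary reporting, and nothing says that either may be claimed as success. The event rate and between-centre variance behind the simulations are assumptions.

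Most of this stands, and it limits the claim. The inflation is conditional on an uncorrected fit, and the two-model figure applies only under an either-counts rule that the protocol does not contain. What remains is that the section fixes the model class and lists covariates, an imputation method and a missingness threshold, yet leaves open the choice on which the 0.05 level depends with 30 centres. An ordinary GLMM run exactly as described would tend to exceed that level.

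**Conclusion.** The point holds in conditional form. With one uncorrected ML GLMM on 30 centres, the type I error is about 6–9% with Wald z and about 5.5–7% with a likelihood-ratio test, and intervals are slightly too narrow. This rests on a two-sided test, the assumed rates and between-centre variances, and a test that the protocol does not name.

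A reader might infer that the trial's true type I error is 7% or more. The document does not support that. A z cut-off with an unbiased variance gives 6.0%, some ML simulations fell between 6% and 7%, and an adequate correction gives about 5%. Nor should the two-model inflation (about 6.5–8.4%) be added as though it were planned; it is a separate and hypothetical risk.

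The missing ranking of the two estimates is a real ambiguity whatever the size of the inflation. This is a worthwhile, inexpensive improvement and not evidence of an invalid design.

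**What to change.** In section 3.6.2.1:

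- Base the primary test and interval on a restricted or bias-corrected between-centre variance **and** a t reference with centre-based degrees of freedom (at most 28; 26 if the strata are fitted). Alternatively, use a permutation test of centre labels within the visit-volume strata, which mirrors the randomisation in section 3.4.2.
- Apply the same approach to the secondary outcomes.
- Name one model, unadjusted or adjusted, as deciding and the other as supportive. Fix the deciding model's covariates in advance. If it is the adjusted one, the 20% missingness rule must not be able to remove a covariate such as baseline eGFR after the data are seen.

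If the statistical analysis plan already settles these items, a cross-reference is enough. The wording should be settled before the 36-month outcome data are examined.

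The cost is wording and somewhat wider intervals: on 28 df, 2.048/1.960 = 1.045 from the reference distribution and √(30/28) = 1.035 from the variance, about 8% together against an ML Wald z interval. On the 3-year Poisson reading, power falls from about 93.4% with z to 91.7% with t on 28 df, still above the stated 90%.

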##### 3.1.2 CKD Patients

###### 3.1.2.1 Inclusion Criteria

1. Age $\geq$ 18 years

- 
2. Diagnosis of CKD, defined as meeting at least one of the following criteria:
- (1) Two estimated glomerular filtration rate (eGFR) values  $<60 \text{ mL/min/1.73m}^2$  (calculated using the CKD-EPI equation), obtained  $\geq 90$  days apart.
  - (2) Confirmed proteinuria, defined as two positive results  $\geq 90$  days apart for either urine albumin-to-creatinine ratio (UACR)  $\geq 30 \text{ mg/g}$ , urine dipstick  $\geq 1+$ , or 24-hour urine total protein (UTP)  $\geq 150 \text{ mg}$ .
  - (3) Documented CKD diagnostic codes in the EHR, supplemented by at least one qualifying eGFR or proteinuria result meeting the above thresholds.

3. Beijing medical insurance residents.

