### 3.2.1 CDSS

The CDSS will be developed using a Plan-Do-Check-Act framework and will be integrated into the existing EHR system. In the Plan phase, semi-structured interviews with PCPs will be conducted to identify user needs. The Do phase will involve a multidisciplinary team (including nephrologists, technical experts, and PCP representatives) in designing an initial prototype. A pilot study at an independent primary care center will then be conducted as the Check phase, during which the system will be iteratively refined. Finally, the Act phase will consist of evaluating the system's effectiveness and implementation feasibility through the main clinical trial described above. The CDSS is designed to provide non-intrusive, real-time clinical decision support during patient encounters. The key functionalities deployed in the intervention arm include:

1. Automated case identification & risk stratification: The system automatically identifies patients with or at risk of CKD through structured diagnostic codes and laboratory data.

2. Renal referral for patients without prior diagnosis of CKD

- (1) Rapid decline in renal function meeting the AKD criteria (**Table 3**).

- (2) Presence of refractory hypertension: defined as blood pressure (BP) >140/90 mmHg while prescribed  $\geq 3$  antihypertensive medications, or being prescribed  $\geq 4$  classes of antihypertensive medications.

- (3) Persistently proteinuria, hematuria or eGFR <60 mL/min/1.73m^2 (two consecutive abnormal results obtained  $\geq 90$  days apart)

3. Automated CKD staging (stages 1-5)

4. Structured management protocols for diagnosed CKD patients:

- (1) Stage-specific monitoring of renal function (e.g., eGFR, UACR every 3 month).

- (2) Complication management alerts for identification, evaluation and management targets based on thresholds defined as follows: hypertension (BP >130/80 with proteinuria or >140/90 without), CKD-mineral and bone disorder (CKD-MBD) (corrected Ca2+ <2.2 mmol/L; PO4 >1.61 mmol/L), hyperkalemia (K+ >5.5 mmol/L), metabolic acidosis (pH <7.25 or HCO3 <22 mmol/L), anemia (Hb <120 g/L [Male] / <110 g/L [Female]), and dyslipidemia (LDL-C >1.8 mmol/L).

5. Renal referral for CKD patients presenting with following indications:

- (1) Advanced CKD (stage 4-5)

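### The adjusted model for the primary outcome in the CKD cohort includes baseline eGFR but not baseline proteinuria, although patients enter on either; the cost is a small loss of precision, not bias.

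*Protocol*

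**What the plan says.** Protocol section 3.6.2.1 (Analysis Principles) states: "The primary outcome of hospitalization rate will be analyzed using generalized linear mixed models (GLMMs"). It adds that "Both unadjusted and adjusted estimates will be presented", and that "adjusted analyses will include age, sex, comorbidities (including diabetes, hypertension, and cardiovascular disease), and baseline eGFR". Neither estimate is named as decisive. The same section excludes any variable with more than 20% missing values.

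Section 3.1.2.1 defines the CKD cohort as "Diagnosis of CKD, defined as meeting at least one of the following criteria". There are three routes:

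- Route 1, eGFR: "Two estimated glomerular filtration rate (eGFR) values" below 60 mL/min/1.73m², at least 90 days apart. No urine test is required.
- Route 2, proteinuria: "Confirmed proteinuria, defined as two positive results" at least 90 days apart, on UACR, dipstick or 24-hour protein. No eGFR threshold applies.
- Route 3, code: a recorded CKD code, "supplemented by at least one qualifying eGFR or proteinuria result meeting the above thresholds".

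Section 3 takes baseline characteristics from the screening period and describes randomisation as following it.

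**The concern.** eGFR and proteinuria are the two axes on which the protocol itself defines CKD, yet the adjusted model carries only one of them. The either-or entry rule makes this matter more than leaving out an ordinary prognostic variable. Below eGFR 60 a patient may or may not have proteinuria. At 60 or above, the patient is there almost only because of proteinuria; the main exceptions are patients whose qualifying low eGFR was followed by a higher value. Within the cohort the two risk markers therefore work against each other: patients who look safer on eGFR are more often proteinuric. A model with eGFR alone treats a proteinuric patient with eGFR 90 as low risk, and the eGFR slope is flattened.

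At stake is the efficiency of the adjusted estimate. With 15 centres per arm, a chance difference in proteinuria mix is plausible, and the listed covariates remove it only so far as they correlate with proteinuria.

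**Working it through.** **The plan's own figure.** Section 3.6.1 gives 3,240 patients, 30 centres (108 each), ICC 0.02, a 20% reduction from 35.0 per 100 person-years over 36 months, and 90% power. The design effect is 1 + 107 × 0.02 = 3.14. With Poisson rates 0.35 and 0.28, three years per patient and 1,620 patients per arm, z = 0.07 / √(0.63/3 × 3.14/1620) = 3.47. Power is Φ(3.47 − 1.96) = 93.4%, or 91.7% with a two-sided t test on 28 df. The stated power is matched within 2 points on that reading. The stated N is not, since 90% needs about 2,670. Treating 0.35 and 0.28 as proportions gives 67.8%. This is background; the stated 90% is the reference below.

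**Step 1: does the entry rule weaken eGFR?** The protocol gives no joint distribution, so this is simulated under assumptions: a source correlation of eGFR and log UACR between −0.3 and 0; a log-rate effect of −0.2 to −0.3 per 10 mL/min of eGFR and +0.2 to +0.3 per log-unit of UACR; entry if eGFR is below 60 or UACR is 30 mg/g or more.

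- The correlation within the cohort becomes about +0.30 to +0.50.
- Without UACR, a true eGFR slope of −0.20 is fitted at −0.17 to −0.12, and one of −0.30 at −0.27 to −0.22. With UACR the true slopes return.

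**Step 2: what reaches the treatment effect?** Residual individual variance, relative to an unadjusted model, falls from 0.904 (eGFR only) to 0.850 (with UACR) in the weakest case, and from 0.835 to 0.705 in the strongest. That is a drop of 6% to 16%. Variance of a centre mean is 0.02 + 0.98 × r/108, where r is that residual ratio and between-centre variance is held fixed.

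| Case | eGFR only | with UACR | variance ratio | SE ratio |
|---|---|---|---|---|
| Weakest | 0.02820 | 0.02771 | 0.983 | 0.991 |
| Strongest | 0.02758 | 0.02640 | 0.957 | 0.978 |

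The gain is small because 0.02 / (0.02 + 0.98/108) = 69% of the centre-mean variance lies between centres, where an individual-level covariate does not reach unless case mix differs by centre. At 90% power the standardised effect is 1.2816 + 1.96 = 3.2415. Dividing by 0.991 or 0.978 and subtracting 1.96 gives power of 90.5% to 91.2%.

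**Step 3: what if proteinuria prevalence differs between centres?** Assume 60% of the cohort is below eGFR 60, of whom 30% are proteinuric on average, with a between-centre SD of 0.05-0.10; all others are proteinuric; the rate ratio (RR) for proteinuria is 1.5-2. Cohort prevalence is 0.4 + 0.6 × 0.30 = 0.58.

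- Expected events per patient over 36 months are 0.35 × 3 = 1.05.
- Background squared CV of a centre rate is 0.139² + 1/(108 × 1.05) = 0.0281. Here 0.139 is the between-centre CV matching ICC 0.02, from √(0.02/0.98 × 1.05)/1.05.
- Case mix adds [0.6 × SD × (RR − 1) / (1 + 0.58 × (RR − 1))]².
- SD 0.05 and RR 1.5: (0.015/1.29)² = 0.00014, or 0.5% of the total; power goes from 90% to 90.1%.
- SD 0.10 and RR 2: (0.06/1.58)² = 0.00144, or 4.9% of the total; SE ratio 0.975; power goes from 90% to 91.4%.

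This counts only the centre-mix part. A simulation at the trial's size (1,500 runs per scenario, the same ranges of SD and RR), against an eGFR-adjusted model, gave gains of 0.3, 0.6, 0.6 and 3.2 points with proteinuria fully observed. With half of the patients below eGFR 60 not tested, the gains were 0.0, 0.5, 0.2 and 2.0 points. The simulation error of one power estimate near 90% is √(0.9 × 0.1/1500) = 0.8 points, so the smallest gains cannot be told from zero.

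**The case against.** The best case against raising this is that nothing in the plan is invalid. The allocation is randomised, the listed covariates are a defensible prognostic set, and any unlisted prognostic variable invites a similar remark. That stands as to size. It does not dispose of the point, because proteinuria is one of the protocol's own entry criteria and its absence weakens a covariate that the protocol chose.

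A second objection is practical. Patients on route 1 need no urine test, so proteinuria could exceed the 20% missing-data limit and be excluded. That would defeat a simple UACR covariate. It does not defeat a category with a not-tested level, which has no missing values; in the Step 1 type of model the eGFR slope is still restored with that level present. The category does pool three tests whose mix may differ by centre, and it gains less where many patients are untested, as Step 3 shows.

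Four stronger readings are tempting and not supported:

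- A reader might take the flattening of the eGFR slope as the size of the benefit. That slope is a nuisance coefficient; little of the loss reaches the treatment effect.
- A reader might compare proteinuria adjustment with no adjustment and find a larger gain. The relevant comparator is the protocol's eGFR-adjusted model.
- A reader might call this a defect of the primary analysis. The protocol presents both estimates, and only the adjusted one is touched.
- Because the CDSS alerts depend on proteinuria (section 3.2.1: "hypertension (BP >130/80 with proteinuria or >140/90 without"), a reader might want the same covariate in the models for RAASi use, blood-pressure control and referral. Dependence of the intervention on a baseline value does not itself call for adjustment under randomisation, and no calculation here supports that extension.

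**Conclusion.** The point holds as a minor improvement. The adjusted model for the primary outcome in the CKD cohort omits one of the two entry axes, and the either-or rule makes the remaining one a weaker adjuster. There is no bias in expectation.

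The likely gain is 1-2% of the standard error, or roughly 0-1 power point over the eGFR-adjusted model, and up to about 2-3 points if proteinuria prevalence varies materially between centres. All of these sizes rest on assumed effects and distributions, because the protocol gives none. Adjustment for age, diabetes, hypertension and cardiovascular disease was not modelled. Where these correlate with proteinuria, the gain would be smaller still. The mechanism in Step 1 depends less on the exact inputs: its direction was the same across the whole assumed range.

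**What to change.** In section 3.6.2.1, add to the adjusted primary-outcome model for the CKD cohort a baseline proteinuria category with three levels, derived from the screening period: confirmed by the section 3.1.2.1 thresholds; tested and not confirmed; not tested. State that the 20% missing-data exclusion does not apply to it. Because the category is fixed before randomisation and complete for every patient, the not-tested level needs no imputation and introduces no bias between arms.

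The cost is a sentence or two of text, one derived variable from results already extracted to decide eligibility, and two more model parameters. Specifying it now also avoids a post hoc choice of covariate if the arms turn out unbalanced on proteinuria.

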### **3.3.2 Secondary Outcomes**

- 
1. Changes in CKD diagnosis rate: the difference in the proportion of CKD patients with an ICD-code for CKD documentation between the follow-up and baseline periods.
  2. Changes in utilization of renoprotective medications: the difference in prescription rates of RAASi and SGLT2i among CKD patients between the follow-up and baseline periods, reported separately.
  3. Changes in screening rate for CKD: the difference in the proportion of patients at high risk for CKD who complete SCr and/or urine protein testing between the follow-up and baseline periods.
  4. Changes in renal referral rate: the difference in the proportion of CKD patients meeting criteria for nephrologist consultation referral who are actually referred.
  5. Changes in blood pressure control rate: the difference in proportion of CKD patients achieving a target of <130/80 mmHg, based on available tests.
  6. Changes in glycemic control rate: the difference in the proportion of CKD patients achieving a HbA1c <7%, based on available tests.
  7. Changes in lipid control rate: the difference in the proportion of CKD patients achieving a LDL-C <2.6 mmol/L, based on available tests.
  8. Cost-effectiveness of the CKD-CDSS: economic evaluation of the community-based CKD screening and management program.
  9. CDSS implementation process: process evaluation using the RE-AIM framework (**Table 5**) to understand the implementation of this complex intervention. This evaluation examines the factors influencing outcomes across five dimensions—Reach, Effectiveness, Adoption, Implementation, and Maintenance—at both the individual and organizational levels. An initial phase, structured questionnaires for community institutions and physicians (**Table 6**) will be used to inform the timely optimization of the CDSS and its implementation strategy.

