### **3.5.3 Data Security and Quality Control**

The data management team plans to use several security steps to protect information, including firewalls, systems to prevent data leaks, network monitoring, and activity logs. Data quality will be checked during the entire process—from collection and cleaning to merging and updating. Automated tools will be adopted to complete missing values and correct errors to ensure that the data are complete, standardized, consistent, and accurate. A Data and Safety Monitoring Committee (DSMC) carries out regular quality checks, provides feedback, creates quality reports, and helps to resolve any data issues promptly.

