### **3.5.4 Data Usage**

This study will strictly follow national and industry rules for data security. All researchers accessing data are required to sign confidentiality agreements, managed

---

by the DSMC. Electronic audit trails will record all data entries and modifications, including reasons, timestamps, and user identifiers.

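### The 20% missingness rule exempts no pre-specified variable, so as written it could remove test-based secondary outcomes or the baseline eGFR adjustment

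*Protocol*

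**What the plan says.** Protocol section 3.6.2.1 sets two rules by the share of missing values. Below the threshold, "if the proportion of missingness is below 20%, continuous variables will be imputed using regression-based methods and categorical variables using predictive mean matching". Above it, "Any variable with over 20% missing values will be excluded from the analysis". Neither rule separates outcomes from covariates, or pre-specified variables from others.

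The same section adjusts the hospitalization analysis for age, sex, "comorbidities (including diabetes, hypertension, and cardiovascular disease), and baseline eGFR", and presents unadjusted estimates alongside. For the rest: "Other secondary outcomes will be analyzed using the same approach but without adjustment for baseline eGFR".

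Section 3.3.2 defines blood pressure, HbA1c and LDL-C control among CKD patients, each "based on available tests". For HbA1c, the objective in section 2.2.2 covers only patients with diabetic kidney disease, whereas section 3.3.2 covers CKD patients in general.

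Section 3.5.3, on data quality, adds: "Automated tools will be adopted to complete missing values and correct errors". Section 3.5.4 adds: "Electronic audit trails will record all data entries and modifications, including reasons, timestamps, and user identifiers".

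**The concern.** A rule that drops any variable above a cut-off lets the observed data decide whether a pre-specified outcome is reported or a pre-specified covariate is used. The test-based outcomes come from routine records, and the wording of section 3.3.2 itself expects gaps.

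For follow-up outcomes the intervention can influence the result. Section 3.2.1 gives the CDSS stage-specific monitoring prompts and alerts tied to blood pressure and LDL-C, so it may change how many patients are measured and hence which side of 20% an outcome falls on. HbA1c is not named among those alerts, so any such link is less direct there.

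The sections also give three different treatments of an untested patient: leave out, impute, or drop the whole variable. If section 3.5.3 fills values before the 20% is counted, the count understates the true gap. At stake are up to three secondary outcomes and one adjusted estimate.

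**Working it through.** **Figures available.** The protocol states no missingness rate, so there is no figure of its own to reproduce. The planned 3,240 participants (section 3.6.1) serve only as an illustrative denominator. All testing shares and diabetes shares below are assumptions.

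**1. The threshold in patients.** 0.20 × 3,240 = 648. With 647 missing values the variable is imputed; with 649 it is dropped. With exactly 648 neither rule applies, because one says below 20% and the other over 20%.

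**2. HbA1c control.** Let d be the diabetic share of CKD patients, t_d the share of diabetics tested and t_n the share of non-diabetics tested. Then

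missing = 1 − [d·t_d + (1 − d)·t_n].

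With t_d from 0.7 to 1.0 and t_n from 0 to 0.6:

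| d | lowest missing | highest missing |
|---|---|---|
| 0.3 | 1 − (0.30 + 0.42) = 28% | 1 − 0.21 = 79% |
| 0.5 | 1 − (0.50 + 0.30) = 20% | 1 − 0.35 = 65% |
| 0.7 | 1 − (0.70 + 0.18) = 12% | 1 − 0.49 = 51% |
| 0.8 | 1 − (0.80 + 0.12) = 8% | 1 − 0.56 = 44% |

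If all diabetics and no one else are tested, missing = 1 − d, and the outcome is dropped whenever d is below 0.8. In the narrower population of section 2.2.2, missing = 1 − t_d, or 0% to 30% over the same range, and the outcome is dropped only if fewer than 80% are tested. The unreconciled population therefore matters to whether the rule bites.

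**3. Baseline eGFR, CKD cohort.** Section 3.1.2.1 admits patients on proteinuria alone, or on a CKD code plus one qualifying eGFR or proteinuria result. Let s be the share entering without an eGFR criterion and q the share of those with no eGFR on file, and assume everyone else has one. The covariate is dropped if s·q > 0.20, that is q > 0.20/s:

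- s = 0.3: q above 67%
- s = 0.5: q above 40%
- s = 0.7: q above 29%
- s of 0.2 or less: the threshold cannot be passed

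**4. Baseline eGFR, high-risk cohort.** Most entry routes in section 3.1.3.1 (coded disease, BMI, family history, age) need no creatinine. Creatinine and/or urine protein testing in this cohort is itself an outcome to be improved (sections 2.2.2 and 3.3.2). The covariate is dropped if more than 20% have no baseline creatinine. Whether eGFR adjustment applies here is unclear. Section 3.6.2.1 ties it to the primary outcome, and section 3.6.1 defines that as the kidney and cardiovascular composite. Section 2.2.1 nevertheless lists the high-risk hospitalization objective as primary.

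**5. What the intervention can affect.** Section 3 takes baseline characteristics from the screening period, which section 3.1.1 dates from March 2022 to March 2023, before the intervention. The CDSS can change testing during follow-up, but not missingness in baseline eGFR.

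**6. What is not exposed.** Hospitalization, coded diagnosis, prescription, screening and referral are read as presence or absence of a record, so missing values do not arise in the same way. By section 3.6.2.1, losing eGFR affects only the adjusted hospitalization estimate.

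**7. Order of steps.** Section 3.5.3 does not place automated completion before or after the 20% count. If it comes first, the measured share is too low and the rule is less likely to fire. If it comes later, or is not used, the exclusion rule operates on the true gaps. These are alternatives and cannot both occur for the same variable.

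**The case against.** The strongest reply is that section 3.3.2 limits the denominator to tested patients. On that reading an untested patient is outside the outcome, nothing is missing, and the 20% rule never fires for blood pressure, HbA1c or LDL-C. The reading is possible. But section 3.6.2.1 covers any variable and does not defer to section 3.3.2, so the conflict stands.

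It is also fair that the unadjusted primary estimate is pre-specified, that one CKD entry route requires two eGFR values, and that a SAP may hold more detail. The first two points limit the reach of the problem. The third does not answer it, because the protocol states a rule here and does not leave one open.

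A reader might infer several stronger claims that the documents do not support:

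- *That the outcomes will be deleted.* No missingness rate is given. For blood pressure, LDL-C and eGFR in the CKD cohort, crossing 20% is uncertain.
- *That automated completion hides the missingness.* The audit trail in section 3.5.4 should let the original gaps be recovered. The defect is the unstated order.
- *That confidence intervals will be too narrow.* The protocol says regression-based, and specifies neither single nor deterministic imputation. The main outcomes are hospitalization rates and the test-based ones are binary control rates. A calculation for the mean of an imputed continuous variable matches no estimate named in the plan.
- *That predictive mean matching is wrong for every categorical variable.* It can serve for binary or ordered variables; the objection holds for unordered categories.

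**Conclusion.** The concern holds as a defect in a stated rule. As written, section 3.6.2.1 could remove up to three secondary outcomes and the eGFR adjustment, according to the missingness that happens to be observed. The risk is most plausible for HbA1c control over all CKD patients, and for eGFR in the high-risk cohort if it is adjusted for there. It is less certain for blood pressure, LDL-C and eGFR in the CKD cohort. The ranges shown rest entirely on assumed diabetes and testing shares. The firm part needs no assumption: the rule has no exemption, it conflicts with section 3.3.2, it leaves exactly 20% unassigned, and its order relative to section 3.5.3 is undefined. No stated sample size or power figure changes.

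**What to change.** - In section 3.6.2.1, remove the 20% exclusion for every pre-specified outcome and covariate. If it is kept for other variables, say what happens at exactly 20%.
- State one treatment of untested patients for blood pressure, HbA1c and LDL-C that agrees with section 3.3.2, and reconcile the HbA1c population between sections 2.2.2 and 3.3.2.
- Keep baseline eGFR in the adjusted model by multiple imputation, with centre in the imputation model and a method suited to each variable type (not predictive mean matching for unordered categories). Say whether eGFR adjustment applies to the high-risk cohort.
- Restrict section 3.5.3 to recovery or correction from source records, with missingness counted and flagged before any completion.

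The cost is protocol or SAP wording and a little computing. The change should be made before outcome data are examined, since a later choice of which variables to keep would look data-driven.
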